## 1. INTRODUCTION

### 1.1 Background

Hypercholesterolemia is an important risk factor for atherosclerotic cardiovascular disease (ASCVD), including cerebrovascular disease, coronary heart disease, and peripheral arterial disease. For patients with known ASCVD, cholesterol-lowering leads to a consistent reduction in cardiovascular mortality and cardiovascular events in men and women and middle-aged and older patients. Among patients without cardiovascular disease, the data on reduction in atherosclerotic cardiovascular disease events with statin drugs is also well documented. Patients with triglyceride levels of more than 1000 mg/dl are at increased risk of acute pancreatitis [1].

Hypercholesterolemia is diagnosed by a lipid profile, consisting of measurements of total cholesterol, Low-Density Lipoprotein Cholesterol (LDL-C) (estimated or direct), High-Density Lipoprotein Cholesterol (HDL-C), and triglycerides. This condition is treated with lifestyle modifications such as dietary changes, exercise, and smoking cessation, as well as pharmacologic intervention with statin therapy, fibrates, bile acid sequestrants, nicotinic acid, and selective inhibitors of cholesterol absorption [2]. Statin therapy is effective for both primary and secondary prevention for Coronary artery disease (CAD) and improves a number of perioperative outcomes. Significant reductions in cardiovascular morbidity and mortality from lipid-lowering as well as pleiotropic effects have been demonstrated. However, statins are not adequate therapy for patients with elevated lipoprotein and for patients with very high levels of LDL-C, such as those with familial hyperlipidemia [3]. Further, some patients are intolerant of statins and might benefit from alternatives and/or combination therapies and even lower LDL-C levels. [4].

Hypercholesterolemia is a strong determinant of mortality and morbidity associated with CAD and a major contributor to the global disease burden [5]. Hypercholesterolemia (TC > 200 mg/dL) has been reported to have a prevalence of up to 35% in men and 36% in women from South Asian countries [6]. The prevalence of hypercholesterolemia was 53.6% in Sri Lankan population according to research data in 2010 among nationally representative sample of 4451 subjects over 18 years by a multistage random cluster sampling technique [7]. LDL-C is a well-established marker for the occurrence, recurrence, and severity of CAD. It is the co-primary target for lipid-

lowering therapy as per the National Lipid Association recommendations for cholesterol management. Hypercholesterolemia corresponds with an elevated plasma LDL-C level because LDL is the main carrier of cholesterol in plasma [6].

## 1.2 Cinnamon

Cinnamon has two main varieties, *Cinnamomum cassia* (also known as *Cinnamomum aromaticum*) and *Cinnamomum zeylanicum* (also known as *Cinnamomum verum*). *C. zeylanicum* is also known as “true cinnamon” or “Ceylon cinnamon”. *C. zeylanicum* is a small tropical tree that is indigenous to Sri Lanka and Southern parts of India [8]. Sri Lanka produces the largest quantity and best quality of cinnamon. One important difference between true cinnamon and cassia cinnamon is their coumarin content [9]. Coumarins can have potentially toxic effects on the liver due to strong anticoagulant properties [10]. The coumarin content in Ceylon cinnamon is negligible, whereas the coumarin level in cassia cinnamon is much higher and can cause health risks if consumed in larger quantities on a regular basis [9]. In addition to its culinary uses, in native Ayurvedic medicine Cinnamon is considered a remedy for respiratory, digestive and gynaecological ailments. Almost every part of the cinnamon tree including the bark, leaves, flowers, fruits and roots, has some medicinal or culinary use. The volatile oils obtained from the bark, leaf, and root barks vary significantly in chemical composition, which suggests that they might vary in their pharmacological effects as well [11]. It is also generally recognized as safe when used in therapeutic doses. According to the United States Food and Drug Administration (FDA), the amount of cinnamon in commonly found foods are generally safe and well tolerated [12]. Several preclinical *in vivo* studies also have not shown any significant toxic effects of cinnamon [8].

Different parts of cinnamon such as leaves, bark, root bark and fruits have various amount of resinous compounds [13]. Cinnamaldehyde, cinnamate and cinnamic acid are the main resinous ingredients found in cinnamon that increase in quantity when cinnamon ages. Cinnamaldehyde is responsible for its spicy taste and fragrance. Essential oils, such as trans-cinnamaldehyde, cinnamyl acetate and eugenol are found in cinnamon [13].

Table 2: Chemical contents of different parts of cinnamon [14]

| Parts of cinnamon | Dominant ingredient (s)                        |
|-------------------|------------------------------------------------|
| Leaves            | Eugenol: 70.00 to 95.00%                       |
| Bark              | Cinnamaldehyde: 65.00 to 80.00%                |
| Root bark         | Camphor: 60.00%                                |
| Fruit             | trans -cinnamyl acetate 42.00 to 54.00% |
| Buds              | Terpene hydrocarbons: 78.00%                   |
|                   | alpha -Bergamotene: 27.38%              |
| Flowers           | (E)-cinnamyl acetate: 41.98%                   |
|                   | trans-alpha -bergamotene: 7.97%         |

Based on traditional medicine and recent scientific evidence cinnamon and its active ingredients such as cinnamaldehyde, cinnamate, cinnamic acid and eugenol in the forms of aqueous and alcoholic extracts have a variety of therapeutic effects. Certain *in vitro* and *in vivo* trials have mainly shown antioxidant, anti-inflammatory, anti-diabetic, anti-microbial, anti-cancer activities and cholesterol and lipid lowering effect [14].

### 1.3 Risk/benefit Assessment of the study

South Asians including Sri Lankans have a high prevalence of cardiovascular diseases (CVD) and suffer from early-onset CVD compared to other ethnic groups. South Asians have a unique lipid profile which may predispose them to premature CVD [15]. The hypercholesterolemia in South Asians is characterized by elevated levels of triglycerides, low levels of high-density lipoprotein (HDL) cholesterol, elevated lipoprotein(a) levels, and a higher atherogenic particle burden despite comparable low-density lipoprotein cholesterol levels compared with other ethnic subgroups. HDL particles also appear to be smaller, dysfunctional, and proatherogenic in South Asians [15]. Given the consistent findings of increased prevalence, premature onset, and increased mortality from CVD in South Asians, there has been much interest in determining the underlying causes. Conventional risk factors such as hypertension, hypercholesterolemia, diabetes mellitus,

abdominal obesity, metabolic syndrome, and tobacco use have been clearly associated with CVD risk among South Asian populations [16]. Some studies have shown that three in four Sri Lankan adults have some form of dyslipidemia [17]. Recent data from WHO estimated that cardiovascular diseases account for 40% of deaths in Sri Lanka [18]. It is estimated that 25.4% of Sri Lankan adults are at high risk for cardiovascular disease [19]. Dyslipidemia is a key modifiable risk factor for cardiovascular disease and data on its prevalence in the country and region were scarce [17].

Among most of the plant based traditional medicines ‘true cinnamon’ plays a key role as a hypolipidemic agent. Several pre-clinical and clinical trials have conducted on this and have shown potential beneficial effects of ‘true cinnamon’. A study conducted by Hasan et al. [20], has demonstrated that *C. zeylanicum* reduced total cholesterol, LDL cholesterol and triglycerides while increasing HDL-cholesterol in diabetic rats. Similar results have also been observed in hyperlipidaemic albino rabbits [21]. A study conducted using hyperlipidaemic albino rabbits showed that *C. zeylanicum* bark powder methanol extract equivalent to 0.75g/kg bark powder and simvastatin (0.6 mg/kg b. wt.) were equieffective in treating hyperlipidaemia [22]. Also, another study conducted using hyperlipidemic albino rats showed a significant ( $p<0.05$ ) hypolipidemic effect on cholesterol and triglycerides of cinnamon extract in groups administered 250 and 500 mg/kg compared with the negative and positive control group. Additionally, the hepatic histopathological study showed that the cinnamon ethanol extract has preventive effect from liver fatty infiltration and granular degeneration [23].

A phase I clinical trial conducted by Ranasinghe et al., [24] has demonstrated that there is a beneficial anti-hyperlipidaemic and blood pressure lowering effects among healthy adults. It had also shown that there are no significant toxic effect or serious adverse effects of true cinnamon (*C. zeylanicum*) other than dyspeptic symptoms. Also, that capsules with 500mg of Cinnamon is safe for ingestion and no side effects were reported in the participant cohort. Jain G S et al. [25] reported that a single supplement intervention with 3 g cinnamon for 16 weeks resulted in significant improvements in all components of metabolic syndrome in a sample of Asian Indians in north India. Khan A et al. [26] investigated whether cinnamon improves blood glucose, triglyceride, total cholesterol, HDL cholesterol, and LDL cholesterol levels in people with type 2 diabetes in Pakistan. They found that after 40 days, all three levels of cinnamon (1, 3, and 6 g) reduced the

mean fasting blood sugar (FBS) (18–29%), triglyceride (23–30%), LDL cholesterol (7–27%), and total cholesterol (12–26%) levels.

*C. zeylanicum* has also been shown to have hepato-protective effects in a study where liver injury was induced in rats by CCl4 [27]. Administration of *C. zeylanicum* extracts (0.01, 0.05 and 0.1 g/kg) for 28 days significantly reduced the impact of CCl4 toxicity on the serum markers of liver damage (AST, ALT and ALP). Also, Askari F et al [28] conducted a double-blind, placebo-controlled trial in Iran with two parallel groups to receive daily supplementation with either two capsules of cinnamon (each capsule contain 750 mg cinnamon) or 2 placebo capsules, daily for 12 weeks. Study has shown that 1.5 g of cinnamon supplementation for 12 weeks improved Nonalcoholic fatty liver disease (NAFLD) characteristics and could be a good adjuvant therapeutic option for NAFLD.

Thus, true cinnamon bark extract can be considered as a therapeutic agent for hypercholesterolemia with comparatively less side effects.

#### 1.4 Rationale

Although certain *in vitro* and *in vivo* studies and very few clinical trials have suggested *C. zeylanicum* seems to lower serum lipid levels, suggesting beneficial cardiovascular effects, it was noted the absence of properly conducted randomized controlled human trials, to decide the lipid lowering effect of *C. zeylanicum* in humans and to determine whether these effects have any other health implications. Thus, this double blinded, placebo-controlled study will be conducted to evaluate the potential effects of *C. zeylanicum* extract in individuals with hypercholesterolemia in Sri Lanka whose LDL level is between 100 mg/dL-190 mg/dL (100 mg/dL < LDL < 190 mg/dL). As per AHA (2018) guidelines, anyone with LDL level >190mg/dL should be started with statins. For any individual with LDL level  $\geq 70$ mg/dL <190mg/dL and without diabetes mellitus, statins will be prescribed only after doing a risk assessment. Thus, the upper cut off will be considered 190 mg/dL. The optimum LDL level is considered as <100 mg/dL and for high-risk individuals (individuals with diabetes or MI) is considered as <70mg/dL. Since people in high-risk category are excluded, the lower cut off was considered as 100mg/dL.

As per AHA (2018) guidelines, since LDL level is considered as the primary parameter in prescribing statins, only LDL level will be considered as an inclusion criterion. Total cholesterol

and triglycerides levels will be not considered as inclusion criteria in recruiting participants into the study.

For triglycerides, the level  $\geq 500$  mg/dL is considered as very high level that can cause acute pancreatitis. However, considering the risk factors that can be associated with high level of triglycerides, anyone with triglyceride level  $\geq 300$ mg/dL will be excluded from the study. This step will be taken to prevent recruiting any participant with a triglycerides level  $< 500$  mg/dL but need to be on a lipid lowering drug based on the clinical assessment.

Further to above criteria, if the investigator decides that a particular person is in need of an immediate lipid lowering therapy (statin) based on his/her clinical judgement, such participants will also be excluded and he or she will be directed to proper medication regime. Thus, high risk participants who are in need of immediate statin therapy will not get deprived of those drugs.

The use of placebo in this type of design has an important value, as “placebo response” is widely known to occur during clinical studies. The addition of a placebo arm is important, as this enables a control for potential influences derived from overall medical care. Therefore, the inclusion of a placebo arm in this study is necessary to prove efficacy of Cinnamon capsule.

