#### 3.2 Exclusion Criteria

Subjects who meet any of the following exclusion criteria are not to be enrolled in the study.

- Participants with an allergy to cinnamon
- Already on cinnamon or any other nutritional / herbal / ayurvedic supplements.
- Lactation, pregnancy or unwillingness to use an effective form of birth control for women of childbearing years
- Any form of malignancy at present or in the past
- Blood dyscrasias
- Estimated Glomerular Filtration Rate (eGFR)  $< 60 \text{ ml/min}$
- Patients with diagnosed alcoholic liver disease (ALD), decompensated cirrhosis or abnormal baseline liver function tests (ALT, AST - Above three times the upper limit of normal)
- Patients with cardiac, liver, renal or respiratory failure (Annexure 01)
- Patients with ASCVD or any other major critical illnesses.
- Any condition that, in the opinion of the primary investigator, would contraindicate the patient's participation

- Currently on statins or any other lipid lowering drug or if investigator decides that the participant is in need of an immediate lipid lowering therapy (statin) based on clinical judgement.
- Participant with triglycerides level  $\geq 300$  mg/dL
- Participants with a history of epilepsy and/or on anti-epileptic drugs

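### The rationale says people with diabetes are excluded, but no eligibility criterion excludes them

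*Protocol*

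**What the plan says.** Section 1.4 (Rationale) of the Protocol explains the LDL entry range. It gives an optimum LDL below 100 mg/dL in general, and says that the optimum "for high-risk individuals (individuals with diabetes or MI) is considered as <70mg/dL". It then derives the lower limit: "Since people in high-risk category are excluded, the lower cut off was considered as 100mg/dL". The same section says that, for LDL from 70 to below 190 mg/dL, prescribing a statin only after a risk assessment applies to people who do not have diabetes.

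Section 1.4 describes two further exclusions. The first is on triglycerides, at 300 mg/dL or more: "considering the risk factors that can be associated with high level of triglycerides, anyone with triglyceride level" at or above that limit is excluded. The second is the investigator's judgement that a statin is needed at once. That paragraph concludes: "Thus, high risk participants who are in need of immediate statin therapy will not get deprived of those drugs".

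Section 3.1 has two inclusion criteria, age 18 to 70 and LDL 100 to below 190 mg/dL. Section 3.2 has thirteen exclusions under the instruction "Subjects who meet any of the following exclusion criteria are not to be enrolled in the study". Those closest to this point are "Patients with ASCVD or any other major critical illnesses", the triglyceride limit, current lipid-lowering treatment "or" the case "if investigator decides that the participant is in need of an immediate lipid lowering therapy (statin) based on clinical judgement", and a general exclusion for any condition the investigator regards as a contraindication. The synopsis repeats the same lists.

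**The concern.** The rationale and the operative criteria describe different populations. Section 1.4 states without condition that the high-risk category is excluded, names diabetes as part of that category, and rests the 100 mg/dL limit on this. Section 3 does not put it into effect.

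What is at stake is participant protection and consistency between sites. Visit 1 (section 4.4.1) has sites judge eligibility against the listed criteria, not against the rationale. A site following the list could enrol a person with diabetes whom a site following section 1.4 would turn away, and that person may receive placebo for three months. The protocol's account of why people in this LDL range can be left off statins pending a risk assessment is itself limited to people without diabetes. Under section 10 the protocol goes to the ethics review committee, which would read in it a categorical exclusion that the criteria do not contain.

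**Working it through.** No arithmetic figure in the plan depends on this point. The check compares section 1.4 with the operative lists.

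**Step 1: what section 1.4 describes, against section 3.2**

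| Ground for exclusion in 1.4 | In 3.2? |
|---|---|
| MI (high-risk category) | Yes, through ASCVD |
| Triglycerides 300 mg/dL or more | Yes, explicit |
| Immediate statin need, investigator's judgement | Yes, explicit |
| Diabetes (high-risk category) | No |

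Three of the four are carried over. Diabetes is the one left out.

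**Step 2: every criterion read for a diabetes rule**

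- Section 3.1: 2 criteria (age, LDL).
- Section 3.2: 13 criteria (cinnamon allergy; cinnamon or other supplements; lactation, pregnancy or no effective contraception; malignancy; blood dyscrasias; eGFR below 60; liver disease or raised ALT/AST; organ failure; ASCVD or other critical illness; investigator's opinion; lipid-lowering drugs or immediate statin need; triglycerides; epilepsy).
- Total: 2 + 13 = 15. Number naming diabetes, FBS or HbA1c: 0.
- Synopsis: 2 + 13 = 15. Number naming diabetes, FBS or HbA1c: 0.

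**Step 3: could another criterion cover diabetes indirectly?**

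- The critical-illness wording sits beside ASCVD and does not naturally reach stable diabetes.
- Annexure 01 is not in the material at hand, but section 3.2 cites it only for cardiac, liver, renal or respiratory failure.
- The statin-need clause turns on immediate need as the investigator sees it. It contains no diabetes or glucose condition.
- The general contraindication clause depends wholly on the investigator's opinion.
- FBS and HbA1c are measured at Visit 1 and are secondary endpoints, but no eligibility rule uses them.

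**Step 4: a case run through the criteria**

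Take a person with diabetes, aged 50, LDL 130 mg/dL, triglycerides 180 mg/dL, no ASCVD, not on a statin, and meeting none of the other exclusions (illustrative values). Both inclusion criteria are met and no categorical exclusion applies. Only the two discretionary clauses could keep this person out. Under section 1.4 the same person belongs to a category said to be excluded.

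**The case against.** The best reply is that section 1.4 never lists diabetes as an exclusion criterion. It mentions diabetes in a parenthesis about LDL targets, and the exclusion appears in a subordinate clause, whereas the triglyceride and statin-need exclusions are announced directly. On this reading the real safeguard is the investigator's judgement. Section 1.4 implies that diabetes moves a person towards statin treatment, Visit 1 gives the investigator the history, FBS and HbA1c, and anyone needing a statin immediately is excluded. The paragraph on that judgement opens with "Further to above criteria, if the investigator decides that a particular person is in need of an immediate lipid lowering therapy (statin", and the criteria it refers back to may be only the LDL and triglyceride limits. The background also cites a trial in type 2 diabetes, so eligibility may be intended.

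Part of this stands. The discretionary route exists and will remove some people with diabetes. The opening phrase of the statin paragraph is not decisive on its own. The numerical limit also does not fail: a person with diabetes and LDL of 100 mg/dL or more is above both optimum levels given in section 1.4.

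It does not close the gap. The sentence that sets the lower limit is unconditional and defines its category by diabetes or MI, not by immediate statin need. If only those needing a statin at once were meant, that sentence is wrong and has to be corrected. If eligibility is intended, the sentence is wrong for that reason. Each reading requires an edit.

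**Conclusion.** The concern holds. Section 1.4 states an exclusion that sections 3.1 and 3.2 and the synopsis do not contain: 0 of 15 criteria in either place name diabetes, FBS or HbA1c, and one of the four grounds described in section 1.4 is missing from section 3.2. For a person with diabetes who is not on a statin and meets no other exclusion, investigator discretion stands where the rationale describes a categorical rule.

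The conclusion assumes that Annexure 01 covers only the organ failures for which it is cited. The number of people affected cannot be estimated from the documents. No bias in the primary analysis is claimed, and the sample size is untouched. It should be fixed because it concerns who may be given placebo.

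**What to change.** If the exclusion is intended, add one line to section 3.2 and the synopsis excluding known diabetes (from the Visit 1 medical history) or a diabetic-range FBS or HbA1c at screening, with the thresholds stated by the sponsor. No new test or visit is needed. History, FBS and HbA1c are already collected at Visit 1, and the eGFR and ALT/AST exclusions already require laboratory results before randomisation. There are two costs: some loss of candidates, whose size the documents do not allow one to estimate, and a narrower population for the FBS and HbA1c secondary endpoints.

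If people with diabetes are meant to be eligible, rewrite the paragraph in section 1.4 so that it no longer says they are excluded. State why the 100 mg/dL limit is kept for them, and justify relying on the investigator's judgement about statins. The cost is one paragraph of text.

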## 1.5 Compliance

This study will be conducted in compliance with this protocol, Good Clinical Practice (GCP), and all applicable regulatory requirements.

## 2. TRIAL OBJECTIVES

The study will evaluate the potential effects of a standardized *Cinnamomum zeylanicum* extract on serum cholesterol levels

### Primary Objective

Primary objective of this study is

- To evaluate the effect of a standardized *C. zeylanicum* extract on LDL levels in individuals with average LDL level between 100-190 mg/dL ( $100 \text{ mg/dL} \leq \text{LDL} < 190 \text{ mg/dL}$ )

## **Secondary Objectives**

Secondary objectives of the study are

- To evaluate the effect on other lipid profile parameters (HDL, total cholesterol and triglycerides)
- To evaluate the effect on sugar levels (FBS, HbA1c)
- To evaluate the effects on anthropometric parameters (weight, waist circumference (WC), hip circumference (HC), mid arm circumference)
- To evaluate the effect on systolic blood pressure (SBP), diastolic blood pressures (DBP).
- To assess the potential effects of regular administration of *C. zeylanicum* extracts on liver and kidney function and the occurrence of self-reported side effects in individuals under study.

